## Abstract

**Background:**

This paper describes the study protocol, the recruitment, and base-line data for evaluating the success of randomisation of the PRO-AGE (PRevention in Older people – Assessment in GEneralists' practices) project.

**Methods/Design:**

A group of general practitioners (GPs) in London (U.K.), Hamburg (Germany) and Solothurn (Switzerland) were trained in risk identification, health promotion, and prevention in older people. Their non-disabled older patients were invited to participate in a randomised controlled study. Participants allocated to the intervention group were offered the Health Risk Appraisal for Older Persons (HRA-O) instrument with a site-specific method for reinforcement (London: physician reminders in electronic medical record; Hamburg: one group session or two preventive home visits; Solothurn: six-monthly preventive home visits over a two-year period). Participants allocated to the control group received usual care. At each site, an additional group of GPs did not receive the training, and their eligible patients were invited to participate in a concurrent comparison group. Primary outcomes are self-reported health behaviour and preventative care use at one-year follow-up. In Solothurn, an additional follow-up was conducted at two years. The number of older persons agreeing to participate (% of eligible persons) in the randomised controlled study was 2503 (66.0%) in London, 2580 (53.6%) in Hamburg, and 2284 (67.5%) in Solothurn. Base-line findings confirm that randomisation of participants was successful, with comparable characteristics between intervention and control groups. The number of persons (% of eligible) enrolled in the concurrent comparison group was 636 (48.8%) in London, 746 (35.7%) in Hamburg, and 1171 (63.0%) in Solothurn.

**Discussion:**

PRO-AGE is the first large-scale randomised controlled trial of health risk appraisal for older people in Europe. Its results will inform about the effects of implementing HRA-O with different methods of reinforcement.

## Background

The development and implementation of effective interventions to prevent or delay disability in older people is an important public health priority. One promising approach is based on Health Risk Appraisal (HRA). HRA interventions were originally developed in the U.S. and tested in working age adults with the aim of identifying risks and decreasing the rate of premature illness and mortality [1]. Subsequently, HRA was adapted for use in older persons, emphasising health behaviour and preventative care in this age group [2-5]. Multiple controlled trials conducted in the United States addressed short or medium term effects of HRA and showed positive effects on health behaviour and uptake of preventative care in older persons, provided HRA was combined with a system of personal reinforcement (supplemental counselling by a physician, health educator, or other health professional) [3].

Until now, the effects of HRA in older persons have not been evaluated in European settings. The effects of the intervention might be influenced by the characteristics of health care systems or cultural factors that differ between North America and Europe. The PRO-AGE (PRevention in Older people – Assessment in GEneralists' practices) project was carried out in London (U.K.), Hamburg (Germany) and Solothurn (Switzerland) to examine the effects of a HRA for Older Persons (HRA-O) [5-8]. Here we describe the study protocol of the PRO-AGE project, and report findings related to the recruitment process and the randomisation of study participants.

## Methods/Design

The PRO-AGE project took place in three locations: the cities of London (U.K.) and Hamburg (Germany) and selected rural areas of the canton of Solothurn (Switzerland). The overall study protocol is summarised in Figure 1, and the recruitment process is given for each site separately (Figures 2, 3, 4). The study was approved by the regional ethical committees (see Acknowledgment section for details).

**Figure 1 F1:**
[figure not shown]
Overall design of PRO-AGE study at the three participating sites (BADL denotes basic activities of daily living; HRA-O denotes Health Risk Appraisal for Older Persons; Pra denotes Probability of repeated admissions)

**Figure 2 F2:**
[figure not shown]
Recruitment and allocation of older persons in London (U.K.) (BADL denotes basic activities of daily living; HRA-O denotes Health Risk Appraisal for Older Persons; Pra denotes Probability of repeated admissions)

**Figure 3 F3:**
[figure not shown]
Recruitment and allocation of older persons in Hamburg (Germany) (BADL denotes basic activities of daily living; HRA-O denotes Health Risk Appraisal for Older Persons; Pra denotes Probability of repeated admissions)

**Figure 4 F4:**
[figure not shown]
Recruitment and allocation of older persons in Solothurn (Switzerland) (BADL denotes basic activities of daily living; HRA-O denotes Health Risk Appraisal for Older Persons; Pra denotes Probability of repeated admissions)

### Recruitment of general practitioners (GPs)

In London, the criteria for inclusion of general practitioners (GPs) were a known interest in primary care for older people, routine use of computerised practice information systems, and practice location in suburban London. Overall, 4 group practices with a total of 26 GPs were recruited (Figure 2). The independent study centre randomly allocated three group practices (18 GPs) to training in risk identification and preventative geriatrics, and one group practice (8 GPs) to the concurrent comparison group.

In Hamburg, GPs registered in the entire metropolitan area were invited to participate via the newsletter of their regional GP association (BDA-Landesverband Hamburg). Overall, 21 GPs (organised in solo practices) agreed to participate (Figure 3) and the Hamburg study centre formed seven groups of three GPs matched for physician age, gender, and qualification (family practice versus internal medicine). In each group of three practitioners, the Hamburg study centre allocated two GPs to training and one GP to the concurrent comparison cohort.

In Solothurn, the cantonal authority selected three mainly rural primary care service areas. The Solothurn study centre obtained agreement to participate from all 33 GPs practising in these pre-selected areas (Figure 4). In each project area, these GPs (mostly organised in single-handed or small group practices) collaborated in practice circles consisting of 8 to 14 GPs each. Each practice circle had monthly meetings to organise emergency care in the region, to exchange practice policy information, and for continuing education. The independent study centre randomly allocated two practice circles to training and those from the remaining circle to the concurrent comparison group.

### Recruitment of older persons

Participating GPs recruited older persons to the project in four steps (Figure 1). Firstly, all practices generated lists of their older patients. The age cut-off for listing patients was based on the country-specific age used for planning and delivery of services to the elderly. In London and Solothurn, an age cut-off of 65 years was selected, in Hamburg a cut-off of 60 years. In a second step, practices were asked to exclude patients meeting the following exclusion criteria: needing human assistance for performing basic activities of daily living or living in a nursing/residential home (in Germany, nursing care according to the German long-term care insurance system); cognitive impairment (i.e. possible dementia, equivalent to a Mini Mental Status score of 24 or less [9]; terminal disease; and/or inability to speak the regional language. In a third step, GPs sent an invitation letter to all individuals remaining on the list. The invitation included an information sheet describing the planned project, the Pra (Probability of repeated admissions) questionnaire [10,11], and a self-administered question on self-perceived need for human help in basic activities of daily living [12]. Patients were asked to return the completed questionnaire if they were interested in participating in the study, and to give informed consent according to the policies of the responsible institution. In London and Solothurn patients were asked to complete and return a written consent form. In Hamburg patients were informed that by returning the questionnaire they agreed to participate in the study. All patients were informed that they could withdraw from the project without negative impact on their care. In a fourth step, persons reporting a need for human assistance in performing basic activities of daily living in the questionnaire, those returning an incomplete Pra questionnaire, and those declining participation (by not returning the brief questionnaire or by returning the questionnaire with an explicit statement of refusal) were excluded from the study. The remaining persons were included in the final list of participants in the study.

### Randomisation of participants

Participating patients of GPs who had received the training were randomly allocated to intervention and control groups by the independent study centre using a computer generated allocation sequence. People living in the same household were allocated to the same group. The ratio of allocation of participants to intervention and control groups was 1:1 in the London sample and 1:2 in the Hamburg sample. In the Solothurn sample, a 1:1 randomisation ratio was used in the initial study phase, and then changed to 1:2, resulting in an average ratio of 1:1.6. Variation in randomisation rates was related to budgetary constraints (see sample size calculation), which became apparent after the project was underway. Participants allocated to the intervention group were offered HRA-O with personal reinforcement. Those allocated to the control group received usual care.

Participants of GPs who had not received additional training formed the concurrent comparison group. All patients in this group continued to receive usual care during the study period. GPs in this group received only general project information during the study period, and were offered the training after the end of the project follow-up.

Final inclusion of study participants started in November 2000 and was completed in London in October 2001, in Hamburg in September 2001, and in Solothurn in February 2002.

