Outcome analyses of the randomised controlled study will be conducted for each site separately in keeping with the inter-site variations of reinforcement methods. The main analyses will compare primary and secondary outcomes between intervention and control groups at follow-up. In these analyses, the fact that participants living in the same household were allocated to the same group will be taken into account by adding the information on household membership to generalised estimating equations (GEE) models [26,27]. Subgroup analyses will be used to evaluate whether the intervention effects differ between predefined subgroups of the population. Firstly, outcomes will be compared between older persons at high risk (Pra > 0.28) and those at low risk (Pra ≤ 0.28) for hospital use [10,11], based on the hypothesis that this type of intervention might have greater positive effects in persons at low risk [28]. Second, for the randomised study in Hamburg and Solothurn, an additional analysis will be carried out to evaluate the independent effects of the site-specific reinforcement on primary outcomes: multivariate regression analyses will be conducted using the composite scores as outcome variables, and participation status in the reinforcement as an independent variable, controlling for intervention allocation status and available participant base-line characteristics. Finally, sensitivity analyses will be conducted to evaluate for potential bias resulting from missing outcome data. First, all analyses will be repeated by adjusting GEE models for base-line age, gender, self-perceived health and number of physician visits reported. Second, primary outcome analyses will be repeated by using with composite scores of health behaviour and use of preventative care which will be derived from imputed outcome estimates in persons with partially missing information.

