### Recruitment and inclusion of study participants

Figures 2 to 4 depict the flow of study participants in London, Hamburg, and Solothurn. As shown, the percentage of participating older persons varied according to study site. Among patients of trained physicians, the numbers of older persons (% of eligible) agreeing to participate were 2503 (66.0%) in London, 2580 (53.6%) in Hamburg, and 2284 (67.5%) in Solothurn. In the concurrent comparison group, the number of persons (% of eligible) agreeing to participate was 636 (48.8%) in London, 746 (35.7%) in Hamburg, and 1171 (63.0%) in Solothurn.

Table 3 lists the results of the analyses comparing age and gender of persons agreeing to participate with eligible patients who declined. This analysis is based on multivariate logistic regression analyses. In London those who declined to participate were on average about one year older than participants. A similar comparison of the recruitment process of the Hamburg randomised study did not reveal statistically significant differences. The interpretability of the Hamburg data is limited because demographic information was not available for a proportion of non-participants due to state-mandated data protection issues. The comparison between participants and non-participants of the Solothurn randomised study revealed a gender difference, with men declining participation more often as compared to women. The comparison between participants and non-participants of the Solothurn concurrent comparison group revealed the same age difference as found in London, with non-responders being approximately one year older as compared to responders.

**Table 3 T3:** Comparison of participants and non-participants in the PRO-AGE study at the three study sites

	**London (U.K.)**			**Hamburg (Germany) ***			**Solothurn (Switzerland)**		
	**Participants**	**Non-participants**	**P-value**	**Participants**	**Non-participants**	**P-value**	**Participants**	**Non-participants**	**P-value**

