### Comparison between groups of participants

Table 4 describes the available base-line characteristics of the study participants according to study sites and group allocation. This is to evaluate the success of randomisation. Within each site, prevalence rates were similar between intervention and control groups. In contrast, there were some relatively minor, but statistically significant differences between persons of the concurrent comparison group and persons of the intervention group (Table 4). Information on education, living alone status, and chronic conditions was derived from baseline HRA-O questionnaire (intervention groups: administered at the start of the project after randomisation; control and concurrent comparison groups: administered at the one-year follow-up). Missing values are due to non-response (all groups) or attrition (death, move away, and move to nursing home) in the control and concurrent comparison groups.

**Table 4 T4:** Self-reported baseline characteristics of the PRO-AGE study participants, according to site and group assignment

**Baseline characteristics**	**London (U.K.)**			**Hamburg (Germany)**			**Solothurn (Switzerland)**		
	**Intervention group**	**Control group**	**Concurrent comparison group**	**Intervention group**	**Control group**	**Concurrent comparison group**	**Intervention group**	**Control group**	**Concurrent comparison group**

Age (years)	74.7 ± 6.4 (1240)	74.4 ± 6.2 (1263)	74.9 ± 6.5 (636)	71.9 ± 7.7 (878)	71.8 ± 7.6 (1702)	72.0 ± 8.2 (746)	74.5 ± 5.8 (874)	74.5 ± 6.1 (1410)	74.2 ± 6.0 (1171)
Female gender	55.3% (686/1240)	54.6% (689/1263)	57.5% (366/636)	61.5% (540/878)	63.3% (1077/1702)	68.2%* (509/746)	56.9% (497/874)	56.5% (796/1410)	57.0% (667/1171)
Fair/poor self-perceived health	24.5% (304/1240)	27.2% (343/1263)	27.4% (174/636)	38.6% (339/878)	38.5 (656/1702)	39.5% (295/746)	19.9% (174/874)	24.8% (349/1410)	23.6% (276/1171)
≥1 hospital admission over past 12 months	14.0% (173/1240)	14.6%) (185/1263)	14.2% (90/636)	21.2% (186/878)	21.2% (360/1702)	22.5% (168/746)	19.9% (174/874)	18.5% (261/1410)	17.7% (207/1171)
> 6 doctor visits over past 12 months	19.0% (236/1240)	24.3% (307/1263)	23.4% (149/636)	49.9% (438/878)	49.9% (849/1702)	44.0%* (328/746)	24.0% (210/874)	24.3% (343/1410)	28.7%* (336/1171)
No available caregiver if needed	17.6% (218/1240)	14.8% (187/1263)	19.2% (122/636)	17.8% (156/878)	18.9% (322/1702)	20.0% (149/746)	9.8% (86/874)	11.6% (163/1410)	8.8% (103/1171)

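### Solothurn moved from 1:1 to 1:2 allocation during recruitment, but no stated model has an allocation-phase term, so the pooled comparison may be partly confounded with time of entry.

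*Protocol article*

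**What the plan says.** Under 'Randomisation of participants', the article gives London a single ratio of 1:1 and Hamburg a single ratio of 1:2. For Solothurn it says that "a 1:1 randomisation ratio was used in the initial study phase, and then changed to 1:2, resulting in an average ratio of 1:1.6". It gives the reason: "Variation in randomisation rates was related to budgetary constraints (see sample size calculation), which became apparent after the project was underway". On timing it states: "Final inclusion of study participants started in November 2000 and was completed in London in October 2001, in Hamburg in September 2001, and in Solothurn"; the closing month for that last site is given as February 2002. Neither the date of the switch nor the arm sizes in each phase are given.

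Under 'Statistical analyses', each site is analysed separately. "The main analyses will compare primary and secondary outcomes between intervention and control groups at follow-up", and the joint allocation of people in one household is handled by "adding the information on household membership to generalised estimating equations (GEE) models". A sensitivity analysis repeats the models with four baseline covariates: age, gender, self-perceived health and number of physician visits. The section closes with simple two-group tests and a GEE with exchangeable within-household correlation. Allocation phase, enrolment date and stratification by ratio appear nowhere, and the Discussion does not list the ratio change among the limitations.

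**The concern.** When the allocation probability changes during recruitment, the arms are comparable by design only among people randomised under the same ratio. In the 1:1 period half of entrants went to intervention; in the 1:2 period one third did. A pooled comparison therefore gives early entrants more weight in the intervention arm than in the control arm. Any difference in outcome level between early and late entrants passes in part into the estimated treatment effect. A larger sample would not remove this.

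Some drift is conceivable from the article itself. Solothurn inclusion ran for up to about 15 months. Some outcomes look back over one year, such as influenza vaccination. The trained GPs cared for both arms and had further training sessions every two to three months, so later entrants may have met more experienced GPs. The Solothurn one-year, two-year, composite-score and Pra subgroup comparisons would all be exposed.

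**Working it through.** **Inputs.** Solothurn randomised total 2284 ('Recruitment and inclusion of study participants'); arms 874 intervention and 1410 control (Table 4); ratios 1:1 then 1:2 ('Randomisation of participants'); control rate 20%, a 30% relative difference (20% to 26%, or 6 points), two-sided 5% level and 20% drop-out ('Sample size/power calculation'). The outcome difference between phases is not in the article and is assumed below.

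**1. The article's own ratio.** 1410 / 874 = 1.61, which agrees with the stated 1:1.6.

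**2. Phase sizes, if the ratios were exact.** Let N1 be the number randomised at 1:1.
- N1/2 + (2284 − N1)/3 = 874, so N1 = 6 × (874 − 2284/3) = 676.
- 1:1 phase: 338 intervention, 338 control.
- 1:2 phase: 1608 people, 536 intervention, 1072 control.
- Check: 338 + 536 = 874; 338 + 1072 = 1410.

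**3. Imbalance in time of entry.** Early-phase share of intervention: 338/874 = 38.7%. Early-phase share of controls: 338/1410 = 24.0%. Difference: 0.147.

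**4. Range for that figure.** Under individual allocation, the standard deviation of the intervention count is √(676 × 1/4 + 1608 × 2/9) = 22.9. N1 could then lie within 676 ± 6 × 1.96 × 22.9, about 406 to 946.
- N1 = 406: expected arms 829 and 1455; 203/829 − 203/1455 = 0.105.
- N1 = 946: expected arms 919 and 1365; 473/919 − 473/1365 = 0.168.

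The factor is therefore about 0.15, range about 0.11 to 0.17. Allocation by household would widen it somewhat.

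**5. Bias and type I error.** With no treatment effect, bias = 0.147 × the between-phase outcome difference. Type I error is by normal approximation, ignoring household clustering. The ranges for 5 and 10 points cover early-phase rates of 20% and 50%, with all participants or 80% evaluable. The 2-point row uses 20% only.

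| Assumed phase difference | Bias (absolute) | Type I error |
|---|---|---|
| 2 points | 0.3 point | about 5.3% |
| 5 points | 0.7 point | about 6-7% |
| 10 points | 1.5 points | about 9-12% |

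Worked case (20% early, 30% late, all analysed): expected rates are 26.1% for intervention and 27.6% for control, difference 1.47 points, SE 1.91 points, ratio 0.77, type I error 12.0%. The 1.5-point bias is a quarter of the planned 6 points. Producing all 6 points would need a phase difference of 0.06/0.147, about 41 points.

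**6. Cost of adjusting.**
- Pooled variance factor: 1/874 + 1/1410 = 0.001853.
- Stratified: phase weights 169 (1:1) and 357.3 (1:2), so 1/526.3 = 0.001900.
- Ratio 1.025, or +1.2% in SE.
- Power for 20% versus 26% with 20% drop-out: about 84.5% pooled, 83.6% stratified.

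**The case against.** The strongest reply has three parts.

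**The article is a summary.** It refers to an a priori analytic plan that is not shown, and a stratum for the allocation ratio could be specified there. That the main model holds nothing beyond arm and household is an inference. It is a fair one, because the article names the one randomisation feature its model respects and lists the covariates of the adjusted model. The ratio change is described but reaches no stated model. The point stands, though the full plan might already settle it.

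**Nothing shows drift.** This is correct. The Solothurn arms agree on age (74.5 in both), gender (56.9% and 56.5%) and the share with more than six doctor visits (24.0% and 24.3%). That is a weak test, since only about 15% of any drift would show. Fair or poor self-perceived health does differ (174/874 against 349/1410, chi-square p about 0.007), and a reader might take this as the mark of the ratio change. It is not evidence of that: London, with one constant ratio, shows a larger contrast in doctor visits (236/1240 against 307/1263, p about 0.001). Self-perceived health is also already in the sensitivity model.

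**The mechanisms are limited.** One-year preventive-care outcomes look back at least a full year, so simple seasonality largely cancels and mainly year-to-year change remains. A staggered order of inviting patients might also be suspected, but the article describes none.

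**Conclusion.** The point holds as a potential and partial confounding at one site. The stated Solothurn models omit a known feature of the allocation, and the pooled estimate carries about 0.15 (0.11 to 0.17) of any between-phase outcome difference. About 85% of such a difference cancels. With assumed differences up to 5 points the effect is small. At 10 points the bias is about 1.5 points and the type I error roughly doubles. These sizes rest on near-exact ratios within each phase and on differences that the article does not report.

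A reader might infer that the ratio change undermines randomisation in Solothurn. The article does not support this: an independent centre used a computer-generated sequence, both arms recruited in both phases, and the switch is attributed to budget, with no sign that it followed outcomes. Nor does the point reach London or Hamburg, which have single ratios and separate analyses. This is a correction that should be made, not a condition for the trial's validity.

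**What to change.** In the analysis plan, add allocation phase (1:1 period or 1:2 period) as a fixed stratum or covariate to every randomised comparison in Solothurn: main GEE, secondary outcomes, two-year outcomes, composite scores and Pra subgroups. Estimating within phase and pooling by inverse variance would also serve. Report the date of the switch, and the arm sizes and baseline characteristics by phase, so that readers can judge any drift. If the full plan already does this, one sentence saying so is enough.

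The phase indicator should be available from the study centre's allocation records. The change needs no additional participants or procedures, and costs about 1% in standard error, or about one percentage point of power at the planned effect.
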